### Data management {19}

Data are entered into electronic case report forms (eCRFs) using REDCap. Questionnaires are entered directly by the participants through the survey function. All other assessments are recorded on paper CRFs and manually transferred to REDCap by trained study personnel.

### Confidentiality {27}

Participant confidentiality is safeguarded through pseudonymization using a unique four-digit ID. Personal identifiers are stored separately in an encrypted, access-restricted file. Only authorized personnel have access to identifiable data, and all study records are handled in compliance with data protection regulations. Anonymized data are used for analysis, publication, and data sharing.

### Plans for collection, laboratory evaluation, and storage of biological specimens for genetic or molecular analysis in this trial/future use {33}

This is not applicable, as no biological specimens are collected.

## Statistical methods

### Statistical methods for primary and secondary outcomes {20a}

Descriptive statistics are presented as means (M), standard deviations (SD), medians (Mdn), interquartile ranges (IQR), frequencies, and percentages (%). The primary outcome, device-based PA (Fibion^®^), and the secondary outcomes, depressive symptom severity (HAMD17, BDI-II) and health-related quality of life (SF-12), will be analyzed using linear mixed models (LMMs) with measurements at T1 and T2 as outcomes. Baseline values of the respective outcomes (T0) will be included as predictors, along with a baseline × time interaction to account for potential changes in baseline influence over time. Fixed effects will include group (CG, IG1, IG2), time (T1, T2), and the group × time interaction, with a random intercept for each participant. For the secondary outcomes, device-based PA at the corresponding time point will additionally be included as a predictor to examine whether changes in these outcomes are associated with PA. Estimated marginal means from the LMMs will be used to compare groups at each time point, with Dunnett’s adjustment applied for comparisons of each intervention group versus control.

Although randomization is expected to minimize baseline imbalance, any clinically relevant imbalances observed will be accounted for in adjusted analyses of the primary outcome.

Continuous predictors (e.g., age, BMI, baseline PA) will be examined for potential nonlinear effects and may be modeled using flexible approaches such as natural splines. Model assumptions, including normality of residuals and homoscedasticity, will be checked, and appropriate transformations or alternative methods will be applied if assumptions are seriously violated.

Baseline CRF will be tested as a moderator by including CRF and its interactions with group and time (CRF × group × time) in the LMMs. Models will first be run without CRF to estimate the overall intervention effect.

Implementation outcomes (reach, dose, fidelity, adaptation) and participant satisfaction will be summarized descriptively. Between-group differences (IG1 vs. IG2) will be explored using independent-sample *t*-tests. All statistical analyses are performed using SPSS and Jamovi [163], with the significance level set at *p*
$$\le$$ 0.05. The completed trial will be reported in accordance with the CONSORT 2025 statement [164].

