### Sample size {14}

Based on the expectation of a weak-to-moderate effect size (*f* = 0.175) for the primary outcome of change in device-based PA, an alpha error probability of 0.05, and a correlation between repeated measures of *r* = 0.50, 29 participants per group (87 in total) are required to achieve 90% power via ANOVA (G*Power 3.1.9.7). The assumed effect size was informed by previously published comparable RCTs [160, 161]. The final sample size is increased by 30% (*N* = 114) to account for anticipated attrition, defined as loss to follow-up with missing primary outcome data. This adjustment aligns with a previously published RCT involving in-patients receiving PA counselling, which reported a dropout rate of 30% [162].

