### Assignment of interventions: allocation

#### Sequence generation {16a}

Participants are randomly allocated in a 1:1:1 ratio to one of two PA coaching conditions (with or without continuous support after post-intervention) or to a control condition receiving general information about health-enhancing PA. The allocation sequence was computer-generated using the Sealed Envelope^™^ randomization service (Sealed Envelope Ltd., London, UK), employing random permuted blocks of 3 and 6. Randomization is stratified by age (< 35 years vs. ≥ 35 years) and sex (male vs. female) to ensure balanced distribution of these variables across the three study arms. The randomization list was prepared by an independent researcher not otherwise involved in participant recruitment, enrollment, or assessment.

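### Randomisation is stratified by age and sex, but the listed primary model has no term for sex and no clear term for age, and observed baseline imbalance selects further covariates

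*Protocol article*

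**What the plan says.** In the protocol article, Sequence generation {16a} states: "Randomization is stratified by age (< 35 years vs. ≥ 35 years) and sex (male vs. female"), in a 1:1:1 ratio and "employing random permuted blocks of 3 and 6". This gives four strata.

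Statistical methods for primary and secondary outcomes {20a} sets out the linear mixed model for T1 and T2:

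- "Fixed effects will include group (CG, IG1, IG2), time (T1, T2), and the group × time interaction", with a random intercept per participant.
- "Baseline values of the respective outcomes (T0) will be included as predictors, along with a baseline × time interaction".
- On additional covariates: "any clinically relevant imbalances observed will be accounted for in adjusted analyses of the primary outcome".
- On functional form: "Continuous predictors (e.g., age, BMI, baseline PA) will be examined for potential nonlinear effects".

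Sex is named in no model. Age is named only in the last of these sentences, as an example.

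**The concern.** Two choices do not fit together.

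First, permuted blocks within age-by-sex strata hold the arms nearly equal on both factors, so differences between strata contribute little to the real sampling variation of an arm contrast. A model without those factors leaves the between-stratum variation in its residual. If the factors are prognostic given the other covariates, the model-based standard error then overstates the uncertainty.

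Second, the only route by which other covariates reach the primary outcome is observed imbalance. In a randomised trial such imbalance is chance; the reason to adjust is prognostic strength. The rule is also unlikely to bring in age or sex, because the design balances them, and it may bring in variables that differ by chance and predict nothing. No candidate list or threshold is given. The standing of the adjusted result next to the primary one is also left open.

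At stake are a modest amount of power and a primary covariate set that is not fully fixed. The trial is open-label, and Data Availability limits access to the final dataset to the sponsor-investigator and the doctoral student who runs daily operations.

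**Working it through.** **1. The plan's own figure.** Sample size {14} gives f = 0.175, alpha 0.05, r = 0.50 and 90% power, hence 87 participants. For the group-by-time interaction with k = 3 groups and m = 3 time points:

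- λ = N·m·f²/(1 − r) = 87 × 3 × 0.030625 / 0.5 = 15.99
- df1 = (k − 1)(m − 1) = 4; df2 = (N − k)(m − 1) = 168
- power = 0.903. At N = 84 it is 0.891, so 87 is the minimum.

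The figure reproduces. It uses no covariates, so the point raised here does not change it.

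**2. Evaluable number.** 114 × (1 − 0.30) = 79.8, about 80, or 27 per arm.

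**3. Unknown input.** Let R² be the share of residual variance in activity, given baseline activity, that age and sex explain. The documents do not give it. Assumed range: 0 to 0.15.

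**4. Formula under intact balance (no dropout).** The reported standard error is too large by the factor 1/√(1 − R²), and actual two-sided alpha is 2[1 − Φ(1.96/√(1 − R²))]. For a test with 90% power when its standard error is right, power falls to Φ(1.960 + 1.282 − 1.960/√(1 − R²)).

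| R² | SE too large by | actual alpha | 0.90 power becomes |
|---|---|---|---|
| 0 | 0% | 0.050 | 0.900 |
| 0.02 | 1.0% | 0.048 | 0.896 |
| 0.05 | 2.6% | 0.044 | 0.891 |
| 0.10 | 5.4% | 0.039 | 0.880 |
| 0.15 | 8.5% | 0.034 | 0.868 |

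These are upper limits, because dropout disturbs the balance within strata.

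**5. Simulation with dropout.** 114 were randomised in stratified blocks of 3 and 6 and about 80 were retained. Two separate sets of runs without the stratification factors gave:

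| R² | null rejection | SE too large by |
|---|---|---|
| 0.05 | 0.047; 0.044 | about 1%; 2% |
| 0.10 | 0.043; 0.044 | about 4%; 2% |
| 0.15 | 0.041; 0.040 | about 5%; 5% |

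For an assumed effect of 0.65 SD, adding age and sex raised power by about 1 to 2, 3 and 6 points at R² = 0.05, 0.10 and 0.15. At R² = 0 it cost at most about 1 point.

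**6. Cross-check with 87 retained** (ANCOVA at one time point, 6,000 null runs and 3,000 runs with an assumed effect of 0.6 SD):

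| R² | mean SE / true SD, factors omitted | alpha omitted → included | power omitted → included |
|---|---|---|---|
| 0 | 0.2112/0.2104 = 1.004 | 0.049 → 0.047 | 0.794 → 0.793 |
| 0.05 | 0.2114/0.2094 = 1.010 | 0.046 → 0.050 | 0.803 → 0.814 |
| 0.10 | 0.2115/0.2017 = 1.049 | 0.035 → 0.049 | 0.812 → 0.843 |

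The Monte Carlo standard error of a rejection rate near 0.05 is √(0.05 × 0.95/6000) = 0.003, so single entries, such as the 0.035, are noisy. The direction and rough size agree with step 5.

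**The case against.** The case on the other side has real weight.

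- **The consequence is conditional.** A reader might infer that the standard errors are too large as a matter of fact. The documents do not support that. Baseline activity and its interaction with time are already in the model and may absorb most of what age and sex would explain. No residual R² is given, and at zero nothing is lost. This stands.
- **The error is on the safe side.** The omission makes intervals too wide and the test conservative. It neither biases the estimate nor raises the false-positive rate. This stands.
- **Age is not plainly left out.** The sentence on nonlinear effects names age beside baseline activity, which is certainly in the model, so age may be meant to enter. The text is therefore unclear on age. It says nothing comparable about sex.
- **Selective reporting is not shown.** A reader might infer that an adjusted model chosen after seeing outcomes will replace the primary one. The text speaks only of adjusted analyses and does not say that they replace anything. Baseline imbalance can also be judged without outcome data. What remains is that the text does not settle either matter.
- **The effect sizes used for power are not the trial's.** Neither 0.65 SD nor 0.6 SD appears in the documents, so those power figures are illustrative. The planned evaluable number is 29 per group, and the intention-to-treat analysis includes everyone randomised, with imputation. The figure of about 80 is therefore what 30% attrition from 114 leaves with observed data.
- **Covariate lists are often left to an analysis plan.** That would answer a silence. Here the article itself lists the model terms and states the rule for adding covariates, so the point concerns what is written.

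**Conclusion.** The point holds in a limited form. The design stratifies on two factors, the listed primary model contains no term for one and no clear term for the other, and the stated route to further covariates is observed imbalance, with no list and no stated relation to the primary result.

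Over an assumed residual R² of 0 to 15%, with about 80 of 114 evaluable and dropout at random, the standard error is about 0 to 5% too large and actual alpha about 0.05 to 0.04. Including the factors changes power by about 0 to +6 points for an assumed effect of 0.65 SD. The documents do not support a claim of invalid inference, inflated type I error or demonstrated selective reporting. The weakness of choosing covariates by imbalance does not depend on R². This is a free improvement, not a flaw that threatens the trial's conclusions.

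**What to change.** In {20a}, name sex and age (continuous, or as the <35/≥35 stratum) as prespecified fixed effects in the mixed models for the primary and secondary outcomes. Replace the imbalance sentence with a supportive sensitivity analysis whose covariates are fixed in advance on prognostic grounds, and state that it supplements the primary result and does not replace it.

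The cost is two degrees of freedom and a short change of text. Both variables are already recorded for randomisation. If they turn out not to be prognostic, the precision lost is negligible: with 87 retained and R² = 0, the standard error goes from 0.2112 to 0.2119. Trial status schedules data collection until September 2027, so the change can be made before the data are complete.

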## Objectives {7}

Building on the background outlined above, the primary objective of this study is to examine the short- and long-term effects of a novel PA coaching program to promote PA behavior in outpatients with MDD receiving treatment as usual. The intervention consists of a structured PA coaching approach that integrates both affective (interest- and experience-based) and cognitive (reflective) strategies to facilitate the adoption of a sustainable PA routine. To enhance engagement and adherence, participants are also supported through continuous self-monitoring using a commercially available smart ring.

Secondary objectives are (i) to assess short- and long-term effects of the PA coaching program on quality of life and depression severity and (ii) to investigate potential mechanisms responsible for the targeted behavior change.

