## Interventions

### Explanation for the choice of comparators {6b}

By comparing PA coaching interventions (IG1 and IG2) with standard treatment (CG), this study assesses the effectiveness and potential superiority of PA coaching in increasing PA, alleviating depressive symptoms, and enhancing quality of life. Furthermore, the comparison between a 10-week coaching intervention (IG1) and an extended version that includes an additional 6 months of support (IG2) provides insights into the impact of coaching duration on the sustainability of PA engagement, depression severity, and health-related quality of life. The inclusion of standard treatment across all groups ensures a pragmatic, real-world approach, allowing for a meaningful evaluation of the added benefits of PA coaching within routine clinical care.

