## Outcomes {12}

### Primary outcome

#### Device-based PA

The primary outcome is the change in device-measured PA over time, measured using a Fibion® SENS device (Fibion Inc., Jyväskylä, Finland) over 7 consecutive days at the three timepoints. The device is attached to the anterior thigh (centerline, one-third from the distal end) and sealed in a waterproof covering with medical adhesive tape. Participants wear it continuously, 24 h/day, facilitated by its low-maintenance design (no charging required). The sensor records raw triaxial acceleration at 12.5 Hz and classifies PA type (sitting, long sitting, standing, walking, cycling) and intensity (light [LPA], moderate [MPA], vigorous [VPA]) with high accuracy [103]. Reliability and validity have been demonstrated in previous research [104–109]. To enhance data accuracy, participants record their bedtime, ensuring that sleep periods are excluded from analysis to prevent an overestimation of sedentary time. At the end of the 7-day period, participants remove adhesive tape and return the Fibion® SENS device at the day clinic.

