#### Implementation {16c}

After completing the baseline assessment, each participant draws a sealed envelope to determine their allocation. The research assistant who conducts the assessments then informs the participants of their assigned condition.

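### The depression and quality-of-life models adjust for same-visit physical activity, so their group contrasts do not estimate the effect of coaching

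*Protocol article*

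**What the plan says.** Section {20a} describes one form of model for the primary outcome and for HAMD-17, BDI-II and SF-12: "linear mixed models (LMMs) with measurements at T1 and T2 as outcomes", with baseline, baseline × time, group, time, group × time and a random intercept. For the secondary outcomes it adds a term: "For the secondary outcomes, device-based PA at the corresponding time point will additionally be included as a predictor". The stated purpose is "to examine whether changes in these outcomes are associated with PA". The next sentence reads "Estimated marginal means from the LMMs will be used to compare groups at each time point", with Dunnett adjustment for each coaching arm against control.

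The aim these contrasts must serve is in Objectives {7}: "to assess short- and long-term effects of the PA coaching program on quality of life and depression severity". Section {6b} says that the comparison with standard treatment "assesses the effectiveness and potential superiority of PA coaching in increasing PA, alleviating depressive symptoms, and enhancing quality of life".

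**The concern.** Same-visit PA is not a baseline covariate. Section {16c} says "After completing the baseline assessment, each participant draws a sealed envelope to determine their allocation", so everything measured at T1 and T2 follows allocation. The outcomes section says "The primary outcome is the change in device-measured PA over time", so PA is what coaching sets out to alter. The Discussion names increased PA as the means by which mental health and quality of life should improve.

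Two things follow from adjusting for it.

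- **The mediated effect is removed.** The group term compares arms as if they had the same PA. Any benefit that arises because coached patients move more is credited to the PA coefficient.
- **What is left is not protected by randomisation.** The Background lists depressive symptoms, higher BMI and somatic illness as barriers to PA, so PA and mood influence each other and share causes. Conditioning on PA opens a non-randomised path between group and outcome. Adjusting for the baseline score does not close it for causes that act after baseline.

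At stake is a false conclusion that coaching does not help depression or quality of life. The more fully the trial's theory holds, the more of the effect this analysis hides.

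**Working it through.** **1. What the text allows.** The PA sentence comes directly before the sentence on marginal means, and no secondary-outcome model without PA is named. The one instruction to run models first without a term concerns baseline cardiorespiratory fitness. Section {20b} plans nothing beyond the analyses described.

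**2. The plan's own figure.** The plan gives no figure for the secondary outcomes. Its sample size reproduces as a within-between interaction with 3 groups and 3 time points:

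- λ = f²·N·m/(1−ρ) = 0.175² × 87 × 3/0.5 = 15.99
- df = 4 and 168; power = 0.903

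This settles the meaning of f. If both coaching arms gain d SD over control at T1 and at T2, the double-centred cell effects have root mean square (2/9)d. Then f = 0.175 gives d = 0.175 × 9/2 = 0.79 SD.

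**3. Formulas.** Work in SD units of depression, where negative is better; signs reverse for SF-12. Let a be the effect of coaching on PA, b the effect of PA on depression, and c′ the effect not passing through PA.

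- Total effect (model without PA): c′ + a·b
- PA-adjusted contrast, no shared cause: c′
- PA-adjusted contrast, with an unmeasured cause of loading u on each and in opposite directions (PA residual variance 1): c′ + a·u²

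The last line follows because, given group, the shared cause has slope −u on PA. Its contribution u × (−u)(PA − a·group) leaves +a·u² on group.

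**4. Assumed cases.** The documents give no value for b, c′ or u. All values below are assumptions, with u = 0.4 (u² = 0.16). Large-sample simulations (400,000 subjects) are in brackets.

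| a | b | c′ | Total | Adjusted, u = 0 | Adjusted, u = 0.4 |
|---|---|---|---|---|---|
| 0.35 | −0.2 | 0 | −0.07 | 0 | +0.056 (+0.052) |
| 0.35 | −0.4 | 0 | −0.14 | 0 | +0.056 (+0.054) |
| 0.5 | −0.2 | 0 | −0.10 | 0 | +0.080 (+0.082) |
| 0.5 | −0.4 | 0 | −0.20 | 0 | +0.080 (+0.085) |
| 0.35 | −0.2 | −0.2 | −0.27 | −0.20 | −0.144 (−0.142) |
| 0.35 | −0.4 | −0.2 | −0.34 | −0.20 | −0.144 (−0.148) |
| 0.5 | −0.2 | −0.2 | −0.30 | −0.20 | −0.120 (−0.119) |
| 0.5 | −0.4 | −0.2 | −0.40 | −0.20 | −0.120 (−0.125) |

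With c′ = −0.2 and no shared cause, the share lost runs from 0.07/0.27 = 26% to 0.20/0.40 = 50%. With c′ = 0 it is 100%.

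**5. Two further cases, with b = −0.3 and c′ = −0.15.**

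- a = 0.5: total −0.15 − 0.15 = −0.30; adjusted −0.15. With u = 0.4 it is −0.15 + 0.08 = −0.07, or −0.15 + 0.08/1.16 = −0.081 if the shared cause adds to the PA variance. Simulated: −0.075, about 75% lost.
- a = 0.79, from step 2: total −0.15 − 0.237 = −0.39; adjusted −0.15. With u = 0.4 it is −0.15 + 0.126 = −0.02 (simulated −0.025).

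**6. The planned model form at trial size.** This used baseline × time, group × time and a random intercept, with 29 per arm and 150 replicates, a = 0.5, b = −0.4 and no shared cause. The contrast is IG2 versus control at T1.

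- True total −0.40 (c′ = −0.2): −0.42 without PA, −0.21 with PA.
- True total −0.20 (c′ = 0): −0.18 without PA, +0.02 with PA.

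The departures of about 0.02 from the true values are simulation noise.

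**The case against.** The strongest reply is that the PA term has a declared explanatory purpose, to study association with PA, and that the word for adding it suggests a second step on top of a base model already described. On that reading the base model would supply the treatment contrasts, and a fuller protocol or analysis plan might set the order.

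The purpose is legitimate, and the reading is possible. But the text gives the association question no model of its own and takes the marginal means from the mixed models just described, PA term included. The authors did write a without-first step for fitness, in order to obtain the overall intervention effect, and wrote none for PA. The model is positively specified, so this is not detail left to another document.

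Three limits do stand.

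- The primary-outcome model is unaffected, and the sample size rests on PA alone.
- The percentages depend on assumed paths. Coaching would look wholly ineffective only where nearly all its benefit runs through PA.
- Section {20c} plans imputation if data are plausibly MCAR or MAR. Mood records without accelerometry would be lost only if imputation is not used; otherwise their analysis depends on imputed PA. The documents do not say how many such records to expect.

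**Conclusion.** The concern holds. As written, the group contrasts for HAMD-17, BDI-II and SF-12 are conditional on a post-randomisation mediator and do not estimate the effect that secondary objective (i) asks for. They give at best a direct effect outside PA, and not even that if PA and mood share unmeasured causes.

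The existence of the problem needs only two premises, both of which the protocol holds: coaching changes PA, and PA is related to mood. Its size cannot be taken from the documents. Over the assumed ranges the loss without a shared cause runs from about a quarter of the effect to all of it, and a shared cause can reverse the sign. These are illustrations, not forecasts for this trial.

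**What to change.** Remove same-visit PA from the models that give the group contrasts for HAMD-17, BDI-II and SF-12. Use the primary-outcome form: baseline, baseline × time, group, time, group × time, random intercept. Take the marginal means and the Dunnett-adjusted comparisons from that model only.

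Fit the model with PA separately, label it an exploratory association or mediation analysis, and draw no group comparison from it.

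The cost is one changed sentence in section {20a} and one extra model per outcome, with no added data and no patient burden. Data collection is scheduled to end in September 2027, so the change can be fixed before analysis. The trial is open-label, so it should be dated and documented before outcome data are examined.

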In light of these limitations of standard care, exercise has gained increasing attention as a non-pharmacological approach to alleviating depressive symptoms. Compelling evidence suggests that physical activity (PA) interventions produce moderate to large antidepressant effects [32, 33]. The effect of exercise has even been demonstrated to be comparable to antidepressant medication [34], as confirmed by several meta-analyses [35–37]. Furthermore, regular exercise following the treatment period has been found to decrease the rate of relapse by 50% after 6 months [38]. Beyond its antidepressant effects, PA has also been associated with improvements in broader health outcomes, including health-related quality of life [39], cardiovascular risk [21, 40], cognition [41], sleep [42], and potential biomarkers of depression such as cortisol levels [43]. Owing to the well-documented benefits of exercise in the treatment of depression, PA is now recommended as an effective complementary treatment modality in several national and international clinical guidelines [44–48].

Despite strong evidence supporting exercise as a treatment for depression, its inclusion in clinical guidelines, and its adoption by an increasing number of clinics as a standard therapy [49, 50], PA levels among adults with depression remain significantly lower than in the general population. Data indicate that approximately 86% of individuals with depression do not meet recommended PA levels and tend to engage in more sedentary behavior compared to people without depression [51]. Explanations for the discrepancy between the well-established efficacy of PA and actual PA behavior can, on the one hand, be identified within clinical practice: although PA programs are available in almost all psychiatric hospitals in Switzerland, only about one in four patients utilize them [49]. This underutilization reflects a broader trend of PA being insufficiently prescribed to individuals with MDD [49]. Key contributing factors include limited training among treatment personnel, skepticism regarding patient adherence, and a lack of collaboration with exercise specialists [52].

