On the other hand, at the individual level, people with depression face both physical and psychological barriers to engaging in regular PA. Common barriers include (higher levels of) depression symptoms, higher body mass index (BMI), and the presence of somatic comorbidities [53]. In addition, motivational and volitional deficits in all areas of daily life interfere with the aim of engaging depressed patients in more exercise and PA. Individuals with MDD demonstrate fewer action plans, have less maintenance self-efficacy, and are more easily distracted by barriers [54, 55]. These challenges highlight the need for targeted interventions that provide patients with professional support to enable them to overcome barriers and adopt a physically active lifestyle [53, 56, 57]. In addition, it is important to put effort into the promotion of behavioral skills necessary for patients to build up and maintain PA [46, 56].

Given this background, PA coaching has proven to be feasible and well accepted in inpatients with MDD, as demonstrated in a recent RCT [58, 59]. Despite the feasibility and acceptance, no long-term effects on PA behavior were observed [60]. A qualitative evaluation of the intervention identified several participant-reported challenges, including limited contact during predominantly remote coaching sessions held at 2-week intervals and the absence of structured support following the intervention period [61]. These findings highlight the need for strategies that foster sustained PA behavior beyond the duration of the coaching itself.

PA coaching in PACINPAT was based on the motivation-volition (MoVo) process model [62] and behavior change techniques [63], both grounded in social-cognitive approaches to behavior change. Recent advances in exercise psychology emphasize the role of affective as well as cognitive determinants of behavior [64–68]. The Affective-Reflective Theory of physical inactivity and exercise (ART) distinguishes two coexisting processes: an automatic affective valuation and a reflective cognitive process [64]. In MDD, diminished motivation and volition may reduce the impact of the cognitive reflective process on activity decisions [54, 64], making the enhancement of positive affective responses to PA a promising strategy for both initiating and maintaining long-term participation in PA [69–72].

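### The same-visit activity term in the secondary-outcome models mixes stable differences between people with within-person change, so it does not isolate whether changes in depression or quality of life go with activity

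*Protocol article*

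**What the plan says.** The section on statistical methods for primary and secondary outcomes {20a} specifies a linear mixed model for HAMD-17, BDI-II and SF-12. The outcome rows are T1 and T2. The predictors are the T0 value of the same outcome, its interaction with time, group, time and group × time, with a random intercept per participant. For these secondary outcomes, device-based PA at the matching visit "will additionally be included as a predictor to examine whether changes in these outcomes are associated with PA". No PA change score and no split of PA into person mean and deviation is named. Baseline PA appears in that section only as one example of a continuous predictor to be checked for nonlinearity.

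The background section {6a} says that "PA levels among adults with depression remain significantly lower than in the general population" and, on obstacles to activity, "Common barriers include (higher levels of) depression symptoms, higher body mass index (BMI), and the presence of somatic comorbidities".

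**The concern.** The declared question is about change: do these outcomes change together with PA? The predictor is a level, namely how active the person was that week. If people who are habitually more depressed are habitually less active, PA level and outcome level are associated across people even when nobody's mood moves with their activity.

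Two features of the model might be expected to remove this, and neither does. A single T0 score measures usual severity with error, so adjusting for it removes only part of the stable difference. The random intercept is assumed independent of PA, so it does not take out the rest.

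At stake is how a significant PA coefficient will be read. The article's discussion section argues that sustained increases in PA will thereby improve mental health and quality of life. A coefficient produced by stable differences could be taken as support for that argument.

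**Working it through.** **The plan's own figures.** The article gives no error rate for this test. Its nearby figure is the sample size: "29 participants per group (87 in total) are required to achieve 90% power via ANOVA", with f = 0.175, three groups, three visits and "a correlation between repeated measures of" 0.50. For the within-between interaction, λ = N·m·f²/(1 − r) = 87 × 3 × 0.030625 / 0.5 = 15.99 on 4 and 168 degrees of freedom, which gives power 0.903. The figure reproduces. It supplies only the setting here: 114 randomised, and 114 × 0.70 = 79.8, about 80, after the 30% loss the article cites.

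**Inputs.** The test level is 0.05 ({20a}). The repeat correlation of 0.50 comes from the sample size section {14}; using it for the secondary outcomes as well is an assumption. The stable between-person correlation of PA with the outcome, c (absolute size), is not in the article and was varied from 0 to 0.5.

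**How much of the stable part survives the T0 adjustment.** Take PA and outcome with unit variance, half stable and half visit noise, and visit noise in PA unrelated to visit noise in the outcome. Change in the outcome is then unrelated to PA.
- Same-visit covariance of PA and outcome: 0.5c.
- After conditioning on the T0 outcome: 0.5c − 0.5 × 0.5c = 0.25c. Half remains.
- Single-visit PA coefficient: 0.25c / (1 − (0.5c)²). At c = 0.4 this is 0.10 / 0.96 = 0.104 SD of outcome per SD of PA.

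The mean coefficient from simulating the two-visit mixed model at c = 0.4 was 0.083 to 0.085 in size. It is a little smaller because that model also uses the T1–T2 contrast within a person, which carries no association here.

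**Rejection rates.** The planned model was fitted by REML to 5,000 simulated trials per cell (1,500 for c = 0) at repeat correlation 0.5. A coaching effect on PA at T1 and T2 is absorbed by the group terms, so its size does not affect the PA coefficient. Multiples of 5% are in brackets.

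| c | Same-visit correlation (0.5c) | As planned, N = 80 | As planned, N = 114 | Baseline PA and its time interaction added, N = 80 / 114 |
|---|---|---|---|---|
| 0 | 0 | 4.8% (1.0) | 5.0% (1.0) | not run / 4.3% |
| 0.1 | 0.05 | 6.4% (1.3) | 6.5% (1.3) | 5.9% / 5.0% |
| 0.2 | 0.10 | 8.9% (1.8) | 10.3% (2.1) | 6.7% / 6.4% |
| 0.3 | 0.15 | 14.6% (2.9) | 17.6% (3.5) | 8.1% / 8.8% |
| 0.4 | 0.20 | 22.3% (4.5) | 28.6% (5.7) | 10.8% / 12.2% |
| 0.5 | 0.25 | 32.2% (6.4) | 42.6% (8.5) | 14.5% / 18.2% |

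With repeat correlations of 0.3 or 0.8 and c from 0.3 to 0.5, the planned term rejects in 11.1–29.6% of trials (N = 80) and 13.0–39.9% (N = 114).

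**Alternatives under the same null, c from 0.1 to 0.5.** A within-person deviation with the person mean as a separate term rejects in 5.2% (N = 80) and 4.7–4.8% (N = 114) with the mean taken over T1 and T2. With the mean taken over T0–T2, it rejects in 4.5–4.6% at N = 114 (c = 0.3 and 0.5, 1,500 trials). PA change from T0 gives 5.5–5.7% and 5.0%.

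**Power.** For a true within-visit correlation of −0.3 and no stable correlation, the planned term has 72–73% (N = 80) and 85–87% (N = 114). The within-person term has 90–92% and 97–98%.

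**The case against.** The strongest reply is about what is being estimated. The model conditions on the T0 outcome, so change can be read as residualised change given baseline, and the article asks about association with PA, not with change in PA. On that reading the coefficient in the scenarios above is truly non-zero, and rejecting is not a false positive. This stands. What remains is that such a coefficient does not show outcomes moving with a person's own activity.

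Second, the correlation is assumed. The comparison of depressed people with the general population does not fix a correlation inside a trial that enrols only patients with F32 or F33 diagnoses. The passage on barriers supports a direction for depression but no size, and neither passage addresses SF-12. This also stands. A reader might infer from the lower rows of the table that the plan inflates error 3 to 8 times as such. The documents do not support that: the factor is 1 at zero correlation and about 2 at 0.2.

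Third, baseline PA is mentioned in {20a}, and decomposing a time-varying covariate could be left to an analysis plan that is not shown. Baseline PA is not named for these models, and if it were included the factor would still run from about 1.0 to 3.6. The article does state both the predictor and its purpose, so the mismatch between the two can be judged from the text.

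Fourth, the association is small: about 0.1 SD per SD of PA at c = 0.4. That is fair, and it is a reason not to overstate the point.

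**Conclusion.** The point holds as a mismatch between a stated question and the term meant to answer it. The same-visit PA coefficient mixes stable between-person association with within-person change, and the planned adjustments leave part of the stable association in place. If the question is within-person change, the test rejects too often by a factor of about 1.3 at an assumed stable correlation of 0.1, 2 at 0.2, and 3 to 8.5 at 0.3 to 0.5, with repeat correlation 0.5 and N = 80 to 114. At zero correlation there is no excess. If the question is residualised change, the fault is one of interpretation.

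A reader might also infer that the trial's treatment comparisons are compromised. This point does not show that. It concerns the PA coefficient alone and bears neither on the group contrasts nor on the primary outcome. It is a worthwhile correction to a secondary analysis.

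**What to change.** For the association question, specify a separate model for each secondary outcome. Replace the single PA term by two: the participant's PA at the visit minus their own mean over T0, T1 and T2, and that person mean. Read the association with change from the deviation only. Using PA change from T0 as the predictor is an acceptable simpler form. Adding baseline PA as a covariate is not enough. State that the result is reported as an association and not as evidence of a causal pathway, because reverse causation and time-varying confounding remain under either form.

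The cost is a change of wording and one derived variable, since PA is already measured at all three visits. The downsides are that the within-person term drops between-person information and that participants without T0 PA need imputation. In the scenario checked above, power rises. Data collection is scheduled to run to September 2027, so the change can be made before analysis.
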